**Methods:**

A randomised controlled trial comparing a culturally tailored SMS intervention (The Step One Program) with a generic ‘thank you’ message, and a nested qualitative study to further explore the intervention’s feasibility and acceptability. The Step One Program was co-designed using an Intervention Mapping framework and engaging potential consumers in the developmental process. Participants are block randomised (1:1 ratio) and followed up at the completion of the intervention and at 12 weeks post-intervention. The primary outcomes are alcohol reduction (as measured by the Alcohol Use Disorders Identification Test and self-reported alcohol intake), wellbeing (as measured by the Personal Wellbeing Index – Adult), and help-seeking (as measured by the number of alcohol services accessed and frequency of access). Upon completion of the 12-week post-intervention survey, participants in the intervention group were contacted via email regarding a phone interview on intervention acceptability.

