## Research objectives

### Hypotheses

Compared to participants who receive generic ‘thank you’ messages, participants in the Step One Program will report at the end of the intervention (4 weeks) and 12 weeks post-intervention:Significantly lower alcohol intake as measured by the Alcohol Use Disorders Identification Test (AUDIT) and self-report of number of standard drinks consumed in the previous 30 days.Significantly higher wellbeing as measured by the Personal Wellbeing Index – Adult (PWI-A).Significantly higher service engagement as indicated by the number of services accessed and frequency of access.

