#### Alcohol use and severity

Severity of alcohol use is measured using a modified version of the AUDIT, a screening tool developed by the World Health Organisation [43]. The instrument includes ten questions answered on Likert scales assessing three domains: hazardous alcohol use, dependence symptoms, and harmful alcohol use. Questions three to 10 were changed to ask participants about drinking outcomes in the past four weeks at T2 and past 12 weeks at T3 rather than the past year to avoid collecting overlapping data. A score of 0–7 indicates ‘low-risk’ alcohol use; a score of 8–15 indicates a ‘hazardous level’ of alcohol use; a score of 16–19 indicates a ‘harmful level’ of alcohol use; and a score of 20 or more indicates ‘high-risk’ alcohol use. This scale has been validated and successfully used in different populations [43, 44].

Alcohol use is measured by asking participants to report the number of standard drinks they consumed in the previous 30 days. A basic standard drinks chart is included to assist with calculations.

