### Data analysis

All data will be de-identified and coded to ensure participant anonymity and it will stored securely on a password protected computer. Participant names, corresponding identification numbers, and contact information will be kept in a separate password protected file on a secure computer at Deakin University. Only the research team will have access to secured information. Only the de-identified data will be used in the analysis phase and in the summary of main outcomes that will be delivered to participants, any subsequent publications, and conference presentations. A data monitoring committee is not needed for this study as it is a non-therapeutic (behavioural) trial using low-risk procedures, and as such, the study team will be monitoring the data.

Analyses will be conducted using an intention-to-treat (ITT) approach [59], with all randomised participants analysed in their allocated group regardless of the intervention uptake. Every effort will be made to minimise missing data and where appropriate, multiple imputation will be used to handle missing data.

Baseline participant’s characteristics will be compared between the intervention and control group using Chi-squared or Fisher’s exact test for categorical variables, and *t* test or Kruskal-Wallis test for numerical variables. Drop-out bias will also be assessed using the same approach but comparing the baseline characteristics of participants with complete data against those lost to follow-up as a function of treatment group.

The intervention effect during the 12-week follow-up on numerical outcomes will be assessed using linear mixed models including group, time (T1, T2 and T3) and group by time interaction as fixed effects and participant as a random effect.

The feasibility of the Step One Program will be determined by the proportion of individuals who completed the baseline survey and were eligible to participate, how often participants read the SMS messages, how often they respond to Sunday SMS messages, and completion of follow-up surveys. Intervention acceptability will be reported by 1) summarising the multiple choice responses to the intervention acceptability questions in the T2 survey, and 2) performing qualitative analysis of the short answer responses and interviews using simple coding to identify recurring patterns and themes.

We will explore whether changes between T1 and T2 in the primary outcomes are correlated with changes in the potential mediator variables.

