### Power analysis

The target sample size is 50 participants per group. Assuming 20% attrition rate, we estimate to collect complete data from 40 participants in each group. Sample size calculations are based on the only available Australian study of alcohol consumption in this population, the Australian Alcohol and lesbian/bisexual women – insights into culture and emotions (ALICE) study [1], which provides estimates for the AUDIT score. A sample size of 40 participants per group has 84% power for detecting a post-intervention mean change of 4 points in the AUDIT score, when the standard deviation is assumed as 6 for two independent groups, two-tailed test, and significance level 0.05. This sample size will achieve 80% power to detect effect sizes larger than 0.63 for any of the other scores outcomes.

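### The primary 30-day drinks count is analysed by a linear mixed model with baseline as a response; this keeps the type I error but probably loses power

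*Protocol article*

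**What the plan says.** The abstract makes intake primary: "The primary outcomes are alcohol reduction (as measured by the Alcohol Use Disorders Identification Test and self-reported alcohol intake". The first hypothesis repeats this, naming "self-report of number of standard drinks consumed in the previous 30 days" and requiring a comparison at 4 weeks and again 12 weeks after the intervention. The measures section (Alcohol use and severity) defines the item as a personal estimate: "report the number of standard drinks they consumed in the previous 30 days". It is therefore a count that cannot fall below zero.

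Data analysis states one model for all such outcomes: "numerical outcomes will be assessed using linear mixed models including group, time (T1, T2 and T3) and group by time interaction as fixed effects". The only random effect is for participant. Nothing separate is said for drinks: no baseline covariate, link, transformation or variance function.

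Power analysis sizes the trial on AUDIT only: "A sample size of 40 participants per group has 84% power for detecting a post-intervention mean change of 4 points in the AUDIT score". That figure takes an SD of 6 and a two-sided 5% level. The remaining outcomes are covered by one sentence: "This sample size will achieve 80% power to detect effect sizes larger than 0.63 for any of the other scores outcomes". No mean, standard deviation, proportion of zeros or expected reduction is given for drinks.

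**The concern.** Entry requires AUDIT 8 or above with no upper limit, so the sample can run from hazardous to high-risk drinkers. A 30-day total in such a group will probably be right-skewed, with variance rising with the mean. Two features of the stated model then cost power.

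- T1 is a response and group has its own main effect, so the treatment effect is a difference between arms in change from baseline. That uses the baseline less efficiently than a covariate does.
- Participant differences enter as additive shifts. On the raw scale, a few heavy drinkers can then dominate the error term.

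With 40 completers expected per arm there is little slack. The risk is that a real reduction in a primary outcome is reported as a null result.

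**Working it through.** **Inputs from the article.** 40 completers per arm, two-sided 0.05, waves T1 to T3, and the stated fixed and random effects. **Assumed inputs.** Everything about the distribution of drinks: mean 60 per 30 days unless noted, the coefficient of variation (CV), the within-person correlation r, and the size and form of the reduction.

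**1. The plan's own figures reproduce.**
- AUDIT: (4/6) × √(40/2) = 2.981; Φ(2.981 − 1.960) = 84.6% (83.8% with the t distribution), against 84% stated.
- Other outcomes: (1.960 + 0.842) × √(2/40) = 0.626, against 0.63 stated.
- Attrition: 40/(1 − 0.2) = 50.

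**2. Cost of using baseline as a response.** With equal variance σ² at T1 and at one follow-up, a change contrast has per-person variance 2σ²(1 − r). Baseline adjustment gives σ²(1 − r²). The ratio is 2/(1 + r). For r between 0.37 and 0.64 (the range in step 4) it runs from 2/1.37 = 1.46 down to 2/1.64 = 1.22. The change contrast is noisier by 22% to 46%, before any question of link.

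**3. The log link alone, at one time point, ignoring baseline.** Example: CV 0.8, ratio of means 0.7.
- Difference in means: z = 0.3/(0.8 × √(1.49/40)) = 0.3/0.1544 = 1.943; power 49.3%.
- Log ratio: z = 0.357/(0.8 × √(2/40)) = 0.357/0.179 = 1.994; power 51.4%.

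For CV 0.6 to 1.2 and ratios 0.5 to 0.7, the gain never exceeded about 8 points (largest: 65.4% to 73.3%).

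**4. Three waves, baseline a response in both models.** Random-intercept linear model against a log-link negative-binomial random-intercept model, complete data, 2-df group-by-time test. The article does not name the test, so that is also an assumption. The first eight rows use a ratio of 0.70 at T2 and T3.

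| Assumed setting | Linear | Count | Gain (points) |
|---|---|---|---|
| CV 0.59, r 0.46 | 60.5% | 74.9% | 14.4 |
| CV 0.85, r 0.53 | 37.8% | 55.4% | 17.6 |
| CV 1.06, r 0.64 | 32.1% | 56.2% | 24.1 |
| CV 1.00, r 0.37 | 21.3% | 31.3% | 10.0 |
| CV 1.29, r 0.41 | 14.5% | 24.7% | 10.2 |
| Mean 30 | 31.2% | 51.4% | 20.2 |
| Mean 90 | 31.2% | 55.4% | 24.2 |
| Lognormal noise | 31.5% | 59.6% | 28.1 |
| Fixed cut of 15 drinks, floored at 0 | 26.4% | 71.0% | 44.6 |
| Fixed cut of 12 drinks, floored at 0 | 15.4% | 71.6% | 56.2 |
| Only heavier half respond, wider spread | 32.8% | 37.5% | 4.7 |
| Only heavier half respond, narrower spread | 36.5% | 39.3% | 2.8 |
| Ratio 0.70, and 5% stop drinking | 30.2% | 37.3% | 7.1 |
| Near-constant, roughly normal variance | 47.2% | 39.5% | −7.7 |

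The first ten rows rest on 1,000 runs each and the last four on 600, so each power has a simulation standard error of at most √(0.25/600) = 2.0 points. The two fixed-cut rows remove nearly all drinking from light drinkers and are the most favourable to the count model.

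**5. Separating baseline adjustment from the link.** T1 and T2 only, 24 settings with an effect.

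| Analysis | Power across settings |
|---|---|
| Planned change contrast | 16–54% |
| Linear, baseline-adjusted | 22–78% |
| Negative binomial, log baseline, HC3 errors | 27–84% |

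Baseline adjustment alone added 4 to 24 points. The count model then changed power by about −7 to +37 points. The two together beat the planned contrast in all 24 settings, by 8 to 44 points. In a further set of runs where only above-average drinkers responded, the count model ranged from 8 points worse to 4 points better than the adjusted linear model (for example 45.9% against 54.2%).

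**6. Type I error.** In step 4 the linear model held 4.2–6.0% and the count model 5.0–6.6% across the main null settings. In the design of step 5, HC3 errors did less well: separate sets of null runs gave 4.3–6.3%, 5.9–7.3% and about 7–8.5%.

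**The case against.** The article gives the model in one sentence. It does not say that the variance is constant; that is only the default of such a model. A full analysis plan, not shown, could add a transformation or a variance function and still match the text. The authors also foresee non-normal data, since they allow a Kruskal-Wallis test for baseline comparisons. The simulations lean towards gamma-Poisson data and proportional effects, which suit the recommended model. They use complete data, with neither the 20% attrition nor the planned multiple imputation, and no run fitted exactly the T2-and-T3 model proposed below. Where HC3 errors were used, part of the apparent gain comes from their excess type I error.

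Most of this stands and limits the size of the claim. It does not remove the point: for a primary outcome the published method is linear, with baseline as a response, and the loss in step 2 needs no assumption about skew.

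Three stronger readings are tempting, and the documents do not support them.
- *The planned analysis is invalid.* The linear model held its type I error; the cost is power.
- *The missing log link is the cause.* Baseline adjustment supplies a substantial part of the gain, and the link's share depends on who responds and how.
- *The stated power is wrong.* The 84% and 0.63 figures both reproduce; the article makes no distribution-specific power claim for drinks.

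**Conclusion.** The point holds as one of efficiency. For 30-day drinks, the stated model probably gives up power on a primary outcome. Under the assumed distributions at 40 per arm, baseline adjustment alone recovers about 4 to 24 points. A log-link count model usually adds more under proportional or additive reductions, but little, or slightly less than nothing, if only heavier drinkers respond. With near-constant variance it does worse than the planned model, which is unlikely for a drinks total in people with AUDIT 8 or above and no ceiling. The direction of the combined change was stable across the 24 settings of step 5. Its size cannot be fixed from the article, which gives no distribution for drinks.

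**What to change.** For 30-day drinks only, replace the sentence on linear mixed models with wording such as: *Standard drinks in the previous 30 days at T2 and T3 will be analysed by negative-binomial regression with a log link, including arm, time, arm by time, log(baseline drinks + 1) as covariate and a participant random effect. The ratio of mean drinks and the model-based difference in mean drinks will be reported at T2 and at T3.*

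Add two further sentences.
- Inference will be valid in small samples, for example by a re-randomisation test that respects the blocks of 10 or by a small-sample-corrected variance. HC3 errors alone should not be relied on, given roughly 7–8% type I error in some runs.
- A linear mixed model of T2 and T3 adjusted for baseline drinks will be the sensitivity analysis.

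The cost is analysis wording: no new data, visits or participants. Recruitment and data collection were still running when the article was written, so the change could be dated and fixed before outcomes are examined by arm. The downsides are that the main effect becomes a ratio, which must be converted to drinks for readers, and that error control at this sample size needs care. If a separate analysis plan already sets the scale and baseline handling for drinks, the article's sentence should be aligned with it.

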#### Wellbeing

The PWI-A [45] is used to assess general wellbeing. This 7-item scale measures seven domains: standard of living, personal health, achieving in life, personal relationships, personal safety, community-connectedness, and future security. A supplementary item asks about satisfaction with life as a whole. Items are answered on a 10-point Likert scale ranging from 0 (no satisfaction at all) to 10 (completely satisfied). Australian and international research has demonstrated good reliability of the PWI-A [46].

The WHO Quality of Life-BREF (WHOQOL-BREF) [47] is used as it is a comprehensive measure of wellbeing and quality of life. This instrument contains 26 questions measuring four domains: physical health, psychological, social relationships, and environment. In Australia, the physical health, psychological, and environment domains have been found to have acceptable internal reliability, and marginal internal reliability was found for the social relationships domain [48].

#### Service access and engagement

Participants are presented with a list of alcohol reduction services and treatments. These are: a general practitioner (GP), another doctor (e.g. specialist doctor), a nurse from your general practice, another nurse, social worker, counsellor/psychologist/psychiatrist you attended in person, general counselling telephone helpline (e.g. Lifeline [a free 24/7 telephone crisis hotline]), Counselling Online (a free 24/7 online text-based support for individuals affected by alcohol and other drugs), other drug or alcohol telephone helpline, drug or alcohol service you attended in person, drug or alcohol self-help group (e.g. AA), hospital emergency department, police, naltrexone, acamprosate, disulfiram, and other. At T1 they are asked to indicate which ones they are currently accessing. At T2 and T3, the same list is presented and participants indicate how frequently they accessed each service in the past four weeks at T2 and past 12 weeks at T3 (did not use, 1–2 times, 3–5 times, 6–9 times, 10+ times). Participants can list additional services not included in the survey and are asked to indicate whether any of the services are LGBT or SSAW-specific.

#### Resilience

Resilience is measured using the Brief Resilience Scale (BRS) [49], a 6-item scale measuring ability to recover from stress. Each item is answered on a 5-point Likert scale ranging from 1 (strongly disagree) to 5 (strongly agree). Strong internal reliability has been demonstrated in a sample of women with a mean age of 47.3 years [49].

#### Depression, anxiety, and stress

The Depression Anxiety Stress Scales (DASS) is a 42-item scale with three subscales: depression, anxiety, and stress [50]. Items reflect a negative emotional indicator and are answered on a 4-point Likert scale ranging from 0 (did not apply to me at all) to 3 (applied to me very much, or most of the time). Scores of 10 or more on the depression subscale, 8 or more on the anxiety subscale, and 15 or more on the stress subscale indicate higher than ‘normal’ experiences of each subscale. In a non-clinical general sample of adults, strong internal reliability has been found for the subscales and total score [51].

#### Social support

Social support is measured using the Medical Outcomes Study Social Support Survey (MOS-SS), a 19-item scale [52]. The items are answered on a 5-point Likert scale ranging from 1 (none of the time) to 5 (all of the time) and ask questions related to emotional/informational support, tangible support, affectionate support, and positive social interaction. Research has demonstrated sound psychometric properties for this survey [52, 53].

#### Motivation to change

Motivation to change is measured using the Treatment Needs and Motivation Scale (TNMS) [54]. This scale consists of 36 items and five subscales. The current study administered questions from the Problem Recognition, the Desire for Help, and the Treatment Readiness subscales which is a total of 23 items answered on a 5-point Likert scale ranging from 1 (strongly disagree) to 5 (strongly agree). Items from the Pressures for Treatment and Treatment Needs subscales are not included as they were not deemed to be relevant to the current study. The scale items were reworded as the phrase “drug use” was replaced with “alcohol use”. Internal reliability has been demonstrated for the three subscales [55].

#### Community connectedness

Community connectedness is measured using the Connectedness to the LGBT Community Scale [56]. A modified version that was used in the Rainbow Women’s Help-Seeking Study [7] is also included to measure connectedness to the mainstream community. The original scale was modified to remove references to the LGBTI community in New York and instead ask about the LGBT community in general. Both scales contain 7 items answered on a 4-point Likert scale ranging from 1 (strongly disagree) to 4 (strongly agree). Good internal reliability has been demonstrated for the LGBT and mainstream versions in an Australian sample of sexual minority women [7].

#### Intervention acceptability

At T2, intervention group participants are asked questions that were adapted from two separate studies [57, 58]. They are asked: how often they read the SMS messages (always, often, sometimes, rarely); if the times they received the SMS messages were appropriate (yes, no); how satisfied they were with the frequency of the SMS messages (very satisfied to very dissatisfied); how frequently they would have preferred to receive messages (more than twice daily, twice daily, once daily, at least once per week, never); how helpful they found the SMS messages using a 5-point Likert scale ranging from 1 (extremely unhelpful) to 5 (extremely helpful); if they would recommend SMS messages as an intervention for other SSAW (most certainly, probably, not sure, certainly not); and the importance of culturally tailored message content, measured using an author developed question on a 5-point Likert scale ranging from 1 (unimportant) to 5 (extremely important).

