#### Participant recruitment

Recruitment commenced April 24, 2017 and data collection is ongoing. Participants are recruited from four sources:General practice clinics across Australia that are known to have a high SSAW case-load;Nation- and State-wide SSAW community and social networks through email, websites, and social media. General women’s health groups are also contacted to reach SSAW not active in the LGBT community;Participants from the Rainbow Women’s Help-Seeking study (which examined professional and social help-seeking by SSAW) [7], and the ALICE study (which investigated socio-cultural factors which influenced alcohol use, sexual orientation, mental health, and health service use among SSAW) [1], with permission from the University of Melbourne;Public common areas, such as restrooms and community noticeboards.

Individuals enrol in the study by completing the online baseline survey using a link included with all study advertisements. The home page of the survey provides detailed information about the study, what participation involves, that participants can withdraw at any time and if so, they will be requested (but not obligated) to complete a survey containing the primary outcome measures, that it is anonymous, and that all information collected is confidential. It is a requirement to indicate consent before proceeding to the survey. To acknowledge the time taken to participate, participants who complete the final follow-up survey will go into a draw to win one of two $50 retail vouchers.

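### The reading-frequency item cannot record non-reading, and acceptability is described only for T2 responders and T3 completers, so it is probably overstated for all allocated to the intervention

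*Protocol article*

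**What the plan says.** Under Data analysis, the protocol article judges feasibility by four things. One is the share of people completing baseline who were eligible. The other three are "how often participants read the SMS messages, how often they respond to Sunday SMS messages, and completion of follow-up surveys".

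The reading measure comes from the T2 survey, which only intervention participants answer on this topic. Under Intervention acceptability the item is "how often they read the SMS messages (always, often, sometimes, rarely", with no category below 'rarely'. A neighbouring item does go down to zero: "how frequently they would have preferred to receive messages (more than twice daily, twice daily, once daily, at least once per week, never".

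Acceptability has two sources under Data analysis. The first is "summarising the multiple choice responses to the intervention acceptability questions in the T2 survey". The second is "performing qualitative analysis of the short answer responses and interviews using simple coding to identify recurring patterns and themes".

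The Methods paragraph of the Abstract says who is approached for interview: "Upon completion of the 12-week post-intervention survey, participants in the intervention group were contacted via email regarding a phone interview on intervention acceptability". Under Participant recruitment, people who withdraw are told that "they will be requested (but not obligated) to complete a survey containing the primary outcome measures". Acceptability items are not mentioned there.

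**The concern.** There are two separate problems.

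The first is the response scale. Someone who opened none of the messages has no true answer to give. Choosing 'rarely' merges non-readers with occasional readers, and skipping the item removes them from the denominator. Either way, a feasibility measure cannot show its own worst result.

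The second is who supplies the data. Participants who dislike the programme have more reason than others to leave the T2 survey unanswered or to drop out before T3. Those who do not answer T2 contribute no ratings. Those who do not complete T3 are outside the stated interview route. The planned drop-out comparison uses baseline characteristics, so it cannot recover their views.

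The Background states feasibility and acceptability as aims of the trial. The Discussion expects them to inform policy makers, and the Abstract expects the results to show whether message content and frequency should be individually tailored. People who stopped because of content or frequency would hold some of the most useful evidence on that question.

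**Working it through.** **Response options, set side by side**

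- Reading: always, often, sometimes, rarely. There is no zero.
- Preferred frequency: includes 'never'.
- Helpfulness: "how helpful they found the SMS messages using a 5-point Likert scale ranging from 1 (extremely unhelpful) to 5 (extremely helpful", so a negative answer is possible.

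The scale defect is therefore confined to the reading item. For that item it works in one direction: a non-reader who answers is recorded as reading at least rarely.

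**Which feasibility measures are touched**

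- Eligible share: settled before randomisation, not affected.
- Reading: affected by both the scale and T2 non-response.
- Sunday replies: incoming SMS, not dependent on answering T2.
- Follow-up survey completion: a count that itself falls when people disengage.

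One of four is affected.

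**Size of the responder-only problem**

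The article gives no figure for feasibility or acceptability. The only usable inputs are in Power analysis: 50 per group and 20% attrition. These agree with the stated number with complete data: 50 × (1 − 0.20) = 40. That 20% refers to complete data, so using it for T2 response is an assumption.

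Let N be allocated, m responding and k positive among responders. With nothing known about non-responders:

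- lower bound = k / N (all non-responders negative)
- upper bound = (k + N − m) / N (all non-responders positive)

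With N = 50, m = 40 and an assumed responder rate of 85%:

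- k = 0.85 × 40 = 34
- lower = 34/50 = 68%
- upper = (34 + 10)/50 = 44/50 = 88%

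The responder figure could overstate the all-allocated figure by up to 85 − 68 = 17 points, or understate it by up to 88 − 85 = 3 points.

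Other assumed inputs, N = 50:

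| Responding | Positive among responders | Bounds over 50 |
|---|---|---|
| 40 | 24 (60%) | 48% to 68% |
| 40 | 28 (70%) | 56% to 76% |
| 40 | 32 (80%) | 64% to 84% |
| 40 | 36 (90%) | 72% to 92% |
| 45 | 36 (80%) | 72% to 82% |
| 35 | 28 (80%) | 56% to 86% |
| 30 | 24 (80%) | 48% to 88% |

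**Direction**

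If a fraction d does not respond, and the positive rates are p in responders and q in non-responders, the responder figure exceeds the all-allocated figure by p − [(1 − d)p + dq] = d(p − q). It errs upwards only if q is below p. That is likely when non-response goes with disengagement, but the design does not guarantee it.

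**The case against.** A reader might infer that the feasibility and acceptability measures can only err upwards. The documents do not support this. Three of the four feasibility measures are untouched, and low Sunday replies or low survey completion would show as poor feasibility. The other acceptability items allow unfavourable answers, and the bounds above extend past the responder figure on both sides.

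A reader might also infer that 10 of 50 intervention participants are never asked. That misreads the 20%. It concerns complete data, and someone who answers T2 but misses T3 has given acceptability ratings. The Post-intervention (T2) section says the survey is emailed to participants, so a non-responder was asked and did not answer.

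Nor does it follow that the interviews cannot show why people stopped. A T3 completer may have stopped reading or replying and can say so. What the stated route misses is people who left the study before T3.

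Three further points against the concern have weight:

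- Entry requires a response to the welcome email and the test SMS. A person who then read none of the 40 messages and still completed T2 should be rare. If such a person chose 'rarely', a summary of 'always or often' would not change.
- The withdrawal survey is described as containing the primary outcome measures, not as limited to them. The interview timing rests on one sentence in the Abstract.
- Responder-only summaries are usual for descriptive acceptability data, and denominators are often left to the analysis plan.

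These points reduce the importance of the concern but do not remove it. The response options are stated in full and lack a zero, and the interview sentence is a positive statement of when contact is made. Silence about the withdrawal survey's other content and about denominators is not treated here as an error; the suggestions on those points are improvements.

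**Conclusion.** The point holds in a limited form. One of four feasibility measures cannot record non-reading. Acceptability results will describe T2 responders and, for interviews, T3 completers, and will probably overstate acceptability among everyone allocated to the intervention.

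At the illustrative 40 of 50 responding and 85% positive, the possible overstatement is 17 points and the possible understatement 3. The 85% is assumed, and T2 non-response may be smaller than the 20% borrowed from Power analysis. The judgement that the error is probably upward assumes that non-responders find the programme less acceptable than responders do.

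Importance is modest. These are descriptive aims, and no primary outcome analysis, between-group comparison or power figure depends on them.

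**What to change.** 1. Add 'never' to the reading item. Report early and late participants separately for that item, since they will have seen different options.
2. Offer the acceptability items, including reading, on the existing withdrawal survey, still as a request without obligation.
3. Extend the interview invitation to intervention participants who did not complete T3 and have not declined contact.
4. Report reading and acceptability twice: among responders, and over all randomised intervention participants with the lower and upper bounds shown above. This needs no new data and fits the article's intention-to-treat approach.

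The cost is a change to one descriptive item while data collection is under way, a few added items on a survey already in use, and a few extra emails and interviews. The baseline survey already collects email addresses and mobile numbers. The Sunday-reply, survey-completion and eligibility measures need no change on this account.
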